#### Study settings

One of the study sites will be a county level HIV programme, which is an outpatient programme catering for HIV infected individuals and their families from culturally diverse backgrounds within resource poor settings.

The normative data will be collected from 3 primary schools in the resource poor setting in Nairobi County.

The two settings are in the Kenyan capital city of Nairobi which has a high level of literacy (87.1%) with English being the primary language of instruction in the schools [8]. An English version of the BENCI is therefore ideal for adaptation. We will ensure that the level of English being used is basic and understand to the target population by pilot testing.

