#### Instruments description

A socio-demographic questionnaire will incorporate elements such as age, gender and education background among other variables.

A breakdown of measures within each cognitive domain within BENCI is available in Table 1. The BENCI battery was developed using neuropsychological procedures that are valid with regards to the neuropsychological assessment literature which includes DSM V preferred domain assessments [9]. The test has norms for children aged 6–11 years. The test can be administered within 75 min with a 10-min break in between the 14 neuropsychological tests as shown in Fig. 1.

**Table 1 Tab1:** Comparison of domains and tests used in each domain

BENCI (90 min)		Kilifi Toolkit (120 min)	
Domain	Test	Domain	Test
Processing speed	Simple reaction time test (a plus sign of the screen prompts the child to press a key on the keyboard fast)	–	–
Visuo-motor coordination	Visuo-motor test (involves connection of elements/number in a given sequence)	Verbal/visual selective reminding	Self-ordered pointing test—SOPT (Selection of pictures displayed in varying positions on separate sheets in sets of 6, 8, 10, and 12. As each page is turned the subject is required to identify all members of the set, but to point to each item of the set only once. Touching a picture more than once is considered an error)
Sustained attention	Continuous performance test (respondent presses any key every time the required stimulus appears)	Auditory sustained and selective attention Visual sustained and selective attention	Score (the subject is required to place beads on one of two plates only after a special sound is heard on a cassette tape) People search (a stimulus sheet comprising complete and incomplete stick figures is presented. The subject is required to cross out only complete figures, as quickly as possible)

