A pretest of the BENCI will be carried out in order to identify elements that may not be well understood by respondents and problems that may be encountered during the main study. The piloting will be carried out among randomly selected 10 children from a community-based HIV programme. The randomization will be carried out among 8- to 10-year-old who are living with HIV. They will be randomly selected as they come into the clinic for their usual appointments and requested to enroll for the pilot study. The piloting will aid in adapting BENCI in terms of modifying item formats that may not be recognized by respondents, eliminating translation bias among other modifications. In order to improve content validity, inter-rater reliability analysis will be carried out where two raters will review the results of the pretest. One rater will administer the tool amongst the pilot sample, while the other rater will review how the tool is administered and the respondent responds. This work will be qualitative in nature trying to identify and refine the items and their relevance within BENCI.

HIV exposed and unexposed children will be considered as comparative groups—and potentially matched on the patient background characteristics (age and gender). The two comparable groups will be of equal sample sizes which will be calculated using a formula cited in Wittes [12].

In this study sample size computation is based on data from earlier studies in Africa, the $$ \mu_{1} = 184.7 \left( {sd = 63.7} \right)\;{\text{and}}\;\mu_{2} = 200.6 \left( {sd = 68.7} \right) $$ which are derived using KABC-2 between HIV exposed and unexposed [13]. Thus, the assumed pooled standard deviation of the mean difference is approximately (sqrt (68.7^2^ + 63.7^2^)/2) = 66.3. Together with a significance level of 5% and a power of 80%, these result in a total sample size of 544 respondents, 272 in each study arm. So, the study will need to enroll 272 HIV exposed children and 272 unexposed children.

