Respondents will be recruited using random stratified sampling by sex and age. A list of all respondents aged 8–11 years in the HIV program and 8–11 years in the primary schools according to gender will then be extracted from the children data base in the institutions. The children’s caregivers will then be requested to give consent on behalf of the children in the schools and the HIV program. A list of all the children with parental consent will then be compiled in readiness for data collection day. On data collection day, the respondents who agree to participate, will be shown the room with neuropsychological assessment tools and proceed with the demographic questionnaire and later on the neuropsychological tests. The process will take around 90–120 min per child.

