### Data analysis and presentation

Since the data generated by the BENCI will be collected in computerized format, it will automatically be numerically coded with identifiers attached to different respondents and excel sheets will be generated as programmed in the tool. The Kilifi Toolkit subsets data will be manually keyed into Excel sheets after being numerically coded with identifiers that are attached to differentiate the respondents. Descriptive statistics, as well as, frequency distributions will be used to analyze the demographic traits among other characteristics of the HIV uninfected unexposed (control) and HIV infected (experimental) with the aid of SPSS. Intraclass correlation, in the same software, will be used to calculate test–retest reliability. To examine convergent validity, the raw scores of BENCI subtests will be compared to the raw scores of the subtests in Kilifi Toolkit. A confirmatory factor analysis will be used to assess construct validity. The validity indicators will be several alternative fit statistics as recommended by Hu and Bentler [14]: Chi square its degrees of freedom and its significance value (a good fitting model would show a non-significant value); root mean square error of approximation—RMSEA whose cut off is .06 and below; as well as scoring .95 and above in Comparative Fit Index (CFI) and Tucker–Lewis Index (TLI) [14]. Discriminant validity will be assessed by comparing the neurocognitive scores of the control (HIV unexposed uninfected) to the experimental group (HIV infected) as well as checking on the age sensitivity. This will be assessed using Receiver Operating Characteristics (ROC), where area under the curve will indicate the diagnostic accuracy of BENCI i.e. the ability of the BENCI to correctly classify those with neurocognitive deficits from those without. These statistical calculations will be carried out in SPSS and the diagnostic accuracy indicators will be excellent for .90–1; good for .80–.90; fair for .70–.80; poor for .60–.70; as well as, fail for .50–.60 [15]. Descriptive statistics including frequency tables, percentages, histograms and bar graphs will be used to show results, as well as, explain correlations between the variables. A neurocognitive profile curve will be used to show differences in cognitive outcomes between the experimental and control group.

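### No adjustment for age, sex or education is named in the HIV group comparison, although sampling is stratified by sex and age; adjusting would add precision and remove residual imbalance

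*Protocol article*

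**What the plan says.** All references are to the protocol article.

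- **Comparison.** Data analysis and presentation: "Discriminant validity will be assessed by comparing the neurocognitive scores of the control (HIV unexposed uninfected) to the experimental group (HIV infected"). The same sentence then adds a check of how scores respond to age, and the section goes on to ROC and the area under the curve. The Abstract names ANOVA and correlational analyses. Demographic traits are otherwise given only a descriptive role.
- **Sampling.** Procedure for translation measures and data collection: "Respondents will be recruited using random stratified sampling by sex and age".
- **Matching.** The same section says the groups will be "potentially matched on the patient background characteristics (age and gender"). It does not say whether matching will be done, or whether it would carry into the analysis.
- **Sources of the two arms.** Study settings: "One of the study sites will be a county level HIV programme"; the normative data come from three primary schools.
- **Variables collected.** Instruments description: "A socio-demographic questionnaire will incorporate elements such as age, gender and education background among other variables".
- **Sample size.** The procedure section assumes KABC-2 means of 184.7 and 200.6, a pooled SD of 66.3, 5% significance and 80% power; "these result in a total sample size of 544 respondents, 272 in each study arm".

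**The concern.** Two variables are important enough to structure the sampling, and possibly the matching, but no method named for the group contrast uses them as covariates or strata. That has two possible consequences.

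1. **Precision.** Variance explained by age and sex stays in the error term, so the comparison is less precise than the collected data allow.
2. **Imbalance.** Cases and controls come from different institutions. The article does not say that the age and sex strata will be filled in the same proportions in both arms, and the children tested are those whose caregivers consent and who then agree. A remaining difference in age or sex would go into the HIV contrast. Education is neither a sampling stratum nor a matching factor, so nothing in the design balances it.

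The planned difference is small, so a modest imbalance could make up, or mask, a sizeable part of it. What is at stake is whether a difference in BENCI scores can be read as the instrument discriminating by HIV status.

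**Working it through.** **Inputs from the article:** means 184.7 (SD 63.7) and 200.6 (SD 68.7); pooled SD 66.3; 5% level, taken as two-sided because that reproduces the stated size (one-sided gives 215 per arm); 80% power; 272 per arm. These are the only effect-size figures given, and they are for the KABC-2, not the BENCI.

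**Inputs assumed, because the article gives none:** the share of score variance explained by age and sex (R²), the score gain per year of age, and the size of any imbalance between arms.

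**Step 1: reproduce the plan's figure.**
- Difference = 200.6 − 184.7 = 15.9; standardised, 15.9 / 66.3 = 0.24.
- n per arm = 2 × [66.3 × (1.960 + 0.842) / 15.9]² = 272.9, or 273 when rounded up, against 272 stated.
- SE of the difference at 272 per arm = 66.3 × √(2/272) = 5.69.
- Power = Φ(15.9/5.69 − 1.96) = 79.9%.

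The SD of 66.3 is a marginal one, with no reduction for covariates. The sample size therefore already fits an unadjusted comparison.

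**Step 2: power with adjustment at the same 544 children.** The residual SD is 66.3 × √(1 − R²). Covariates are taken as balanced between arms.

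| Assumed R² | Residual SD | Power at 272 per arm | n per arm for 80% |
|---|---|---|---|
| 0 | 66.3 | 79.9% | 273 |
| 0.10 | 62.9 | 83.8% | 246 |
| 0.20 | 59.3 | 87.8% | 219 |
| 0.30 | 55.5 | 91.7% | 192 |

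**Step 3: bias from an age gap.** Bias in SD units = gap in mean age × gain per year, compared with 0.24.
- Gap 0.25 year: 0.25 × 0.3 = 0.075 SD (31%) to 0.25 × 0.5 = 0.125 SD (52%).
- Gap 0.5 year: 0.5 × 0.3 = 0.15 SD (about 62%) to 0.5 × 0.5 = 0.25 SD (104%).
- If both arms fill the age and sex strata in equal proportions, the gap, and so the bias, is close to zero.

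**Step 4: bias from any other covariate, such as education.** Bias in points = correlation with the score × imbalance in SD units × 66.3. The false-positive rate is the chance that |z| exceeds 1.96 when z is centred at bias / 5.69.

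| Assumed correlation | Assumed imbalance | Bias (share of 15.9) | False-positive rate |
|---|---|---|---|
| 0.30 | 0.10 SD | 2.0 (13%) | 6.4% |
| 0.30 | 0.25 SD | 5.0 (31%) | 14.1% |
| 0.45 | 0.10 SD | 3.0 (19%) | 8.2% |
| 0.45 | 0.25 SD | 7.5 (47%) | 25.9% |

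Step 2 assumes balance and Steps 3 and 4 assume imbalance, so the two effects are alternatives and should not be added together.

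**The case against.** **The article is condensed and never calls the comparison unadjusted.** ANOVA can carry age and sex as factors, and a fuller plan may list covariates. This stands as a limit on certainty: the absence of adjustment is inferred from the methods named. It does not remove the point, because the article does choose its methods for this contrast and gives none of the three variables an adjusting role.

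**Age is not ignored.** It is a sampling stratum, a possible matching factor and the subject of a separate check. That is correct, and a reader who inferred that the analysis makes no use of age would be wrong. The check is set beside the group comparison, however, and is not described as adjustment within it.

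**A reader might infer that the study loses power against its plan.** The documents do not support that: Step 1 gives 79.9%. What is forgone is a gain, whose size depends on an R² the article does not give.

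**A reader might infer that age is bound to pass as an HIV effect.** That is not shown either. Stratified sampling within the same 8 to 11 age range may remove most of an age gap. Nor does the article say whether the scores compared between groups are raw or age-normed; it specifies raw scores only for convergent validity, and the battery has norms for ages 6 to 11. Bias is possible, not demonstrated.

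**The aim is psychometric, and covariates cannot cure the difference in setting.** Both statements are true. Known-groups evidence is still easier to interpret when differences in age and sex are taken out. Setting is completely tied to HIV status, so it can only be declared as a limitation.

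**Conclusion.** The point holds as a worthwhile improvement to the analysis, not as a failure of the design. No adjustment for age, sex or education is named, although the first two structure the sampling and all three are collected. The planned power is met without adjustment. Adjusting for age and sex would lift it from 79.9% to about 84%, 88% or 92%, assuming R² of 0.10, 0.20 or 0.30 and balanced covariates.

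Adjustment also protects a planned effect of only 0.24 SD against residual imbalance. The illustrative 31% to 52% for a 0.25-year age gap is the product of two assumptions and shrinks towards zero if strata are filled equally. Education has no protection from the design, so its possible contribution is the less controlled one. No covariate model can separate clinic from school.

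**What to change.** 1. Analyse each BENCI score with a linear model on HIV group, with age (continuous) and sex as covariates. State whether matching will be done and, if so, include the matching strata.
2. Report an age- and sex-adjusted ROC beside the unadjusted one.
3. Add education in a stated sensitivity analysis. It is kept out of the main model because schooling may be partly a consequence of HIV.
4. State under Study limitations that clinic-versus-school setting cannot be separated from HIV status.

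The cost is a little more analysis work, mainly for the adjusted ROC. All the variables are already on the questionnaire, and the sample size and data collection do not change.

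### The ROC analysis separates children by HIV group, but its AUC is read and graded as diagnostic accuracy for neurocognitive deficit

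*Protocol article*

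**What the plan says.** In the protocol article, under Data analysis and presentation, discriminant validity is to be assessed by "comparing the neurocognitive scores of the control (HIV unexposed uninfected) to the experimental group (HIV infected", together with a check of age sensitivity. The next sentence begins "This will be assessed using Receiver Operating Characteristics (ROC), where area under the curve will indicate the diagnostic accuracy of BENCI" and explains that accuracy as "the ability of the BENCI to correctly classify those with neurocognitive deficits from those without". The AUC is then graded on five bands, from excellent at .90 and above down to "poor for .60–.70; as well as, fail for .50–.60".

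The article gives no cut-off, diagnosis or reference test that would define a neurocognitive deficit. The Kilifi Toolkit enters the analysis only for convergent validity, on raw subtest scores.

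The only effect size in the article is under Procedure for translation measures and data collection. It consists of means of 184.7 (SD 63.7) and 200.6 (SD 68.7), "which are derived using KABC-2 between HIV exposed and unexposed". With "a significance level of 5% and a power of 80"% these give "a total sample size of 544 respondents, 272 in each study arm".

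**The concern.** The two classes offered to the ROC are HIV-status groups, but the result is interpreted as if the classes were deficit and no deficit. These are different things: an infected child may have no deficit, and a control child may have one. The stated interpretation therefore does not follow from the stated analysis, whatever the effect size turns out to be.

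The error can run in either direction. If the groups differ modestly in cognition, a battery that detects deficits well would still receive a low diagnostic grade. If the groups differ for other reasons, the AUC rises and would be reported as accuracy for deficit. Design and Study settings place the cases in an HIV programme and the controls in three primary schools, and sampling is stratified only by sex and age, so such differences are possible.

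The sentence introducing the ROC also follows directly on the mention of age sensitivity. A ROC of infected against control children does not assess that.

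**Working it through.** **Inputs.** Means 184.7 and 200.6, SDs 63.7 and 68.7, 272 per group, 5% significance and 80% power, all from Procedure for translation measures and data collection. The bands are from Data analysis and presentation. The lower mean is taken as the HIV group's, following the order in which the article lists the groups.

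**1. The plan's own sample size.** The difference is 200.6 − 184.7 = 15.9. The pooled SD is printed as "sqrt (68.7^2^ + 63.7^2^)/2) = 66.3". With the root taken over the whole mean of variances it is 66.25, which agrees; the brackets as printed would give 46.8. The two-sided formula gives n = 2 × (1.960 + 0.842)² × 66.3² / 15.9² ≈ 273 per group. The stated 272 gives 79.9% power, so the plan's figure is reproduced. The standardised difference is 15.9 / 66.3 = 0.24.

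**2. The AUC implied by that difference.** Under normal distributions, AUC = Φ(difference / √(SD₁² + SD₂²)) = Φ(15.9 / √(63.7² + 68.7²)) = Φ(15.9 / 93.69) = Φ(0.170) = 0.567. This lies inside the fail band.

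**3. Sampling error.** The Hanley–McNeil formula uses A = 0.5674, Q₁ = A/(2 − A) = 0.3960 and Q₂ = 2A²/(1 + A) = 0.4108. With 272 per group,

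SE = √{[A(1 − A) + 271(Q₁ − A²) + 271(Q₂ − A²)] / 272²} = 0.0245.

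- The 95% sampling range is 0.567 ± 1.96 × 0.0245, or about 0.52 to 0.62.
- P(observed AUC < 0.60) = Φ((0.60 − 0.5674)/0.0245) = Φ(1.33) ≈ 0.91.
- P(observed AUC ≥ 0.70) is practically zero.
- In 20,000 simulated studies the mean AUC was 0.567, the SD 0.0244, and 91% fell below 0.60.

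**4. Difference needed to leave the band.** With equal SDs, d = √2 × z(AUC). A true AUC of 0.60 needs d = 0.36 (23.8 points at SD 66.3), and 0.70 needs d = 0.74 (49.2 points).

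**5. What a perfect deficit detector would score.** A test that identified deficit without error, used to separate HIV groups, has sensitivity p₁ (deficit prevalence in the HIV group) and specificity 1 − p₀ (p₀ in controls). Its AUC is 0.5 + (p₁ − p₀)/2. The article gives no prevalences, so these are assumptions:

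| Deficit prevalence, HIV group vs controls | AUC against HIV group |
|---|---|
| 20% vs 10% | 0.55 |
| 30% vs 10% | 0.60 |
| 50% vs 10% | 0.70 |
| 20.4% vs 15.9% (cut-off 1 SD below the control mean, planning figures) | 0.52 |

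**6. Better measurement.** If the source score had reliability 0.9, 0.8, 0.7 or 0.5 (assumed), an error-free version would have AUC 0.571, 0.575, 0.580 or 0.595. Higher reliability alone does not take it out of the fail band.

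**The case against.** *The ROC reference is inferred.* The text never says in so many words that HIV group is the ROC's reference, and a condensed article may leave a deficit definition to the full protocol. If a deficit classification is meant, the 0.57 and 91% do not apply. This is fair as far as it goes. However, HIV group is the only classification named, the ROC sentence refers back to it, and the third objective in the Introduction also frames discriminative validity as a comparison of HIV-status groups (labelled slightly differently there). If another reference was intended, the sentence as printed is still wrong.

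*The effect size is borrowed.* It comes from the KABC-2, in groups labelled HIV exposed and unexposed. A reader might infer that the BENCI is bound to be graded a fail whatever its quality. The documents do not support that. A BENCI score more sensitive to HIV infection could have a true difference above 0.36, and even at the planning difference about 9% of studies would reach 0.60 by chance.

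*Other analyses exist.* The Abstract names ANOVA and correlational analyses for validity, so a comparison of means and a route to age sensitivity are partly present. The BENCI is also judged by intraclass correlation, confirmatory factor analysis and agreement with the Kilifi Toolkit. A reader might infer that a low AUC would condemn the battery, or that the criterion-validity objective fails through this analysis. No rule in the article lets the AUC band decide validity, and the ROC is tied to discriminant, not criterion, validity. This limits the consequences but does not mend the interpretation of the AUC.

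**Conclusion.** The concern holds as a mismatch between analysis and interpretation. On the natural reading of the section, the AUC measures separation of HIV infected from HIV unexposed uninfected children, and it cannot be read or graded as accuracy for neurocognitive deficit. That conclusion does not depend on any effect size.

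The likely practical result does. If the BENCI showed the difference used for the sample size, with normally distributed scores, the AUC would be expected at about 0.57 (SE about 0.025) and graded a fail with about 91% probability, even if the battery detected deficits well. The study is thus sized to find a difference that its own bands would most likely label a failure.

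**What to change.** Under Data analysis and presentation:

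1. Call HIV infected versus HIV unexposed uninfected a known-groups comparison. Report the standardised mean difference, and the AUC if wanted, each with a 95% confidence interval.
2. Delete the neurocognitive-deficit reading and the .50–1 diagnostic bands for that comparison.
3. Assess age sensitivity separately, by relating BENCI scores to age, for example by regression.
4. Keep a diagnostic-accuracy claim only if an independent deficit reference is pre-specified.

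Items 1 to 3 are changes of wording and need no new data.

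For item 4, a definition based on the Kilifi Toolkit would use data already collected, but it has limits. A composite would have to be built from subtests. Table 1 lists no Kilifi test for processing speed or language. The toolkit is an imperfect reference, and the analysis would partly repeat the convergent-validity work.

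Deficit cases would also be few. With an illustrative cut-off 1.5 SD below the control mean, controls contribute 272 × 0.067 ≈ 18. The HIV group contributes 272 × 0.086 ≈ 23 with the separate SDs, or 272 × Φ(−1.5 + 0.24) = 272 × 0.104 ≈ 28 with a common SD. That makes about 41 to 46 of 544. By the Hanley–McNeil formula, an AUC of 0.80 would then have a standard error of about 0.04 overall and 0.05 to 0.06 within the HIV group.
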